**Methods:**

Patients diagnosed with OSA and meeting the eligibility criteria will be randomly allocated in the groups. The experimental group will receive comprehensive rehabilitation, and the control group will receive myofunctional therapy. CPAP will be continued by all the participants. Both the groups will receive the interventions for 12 weeks. The primary outcome measures are AHI and Epworth Sleepiness Scale (ESS), and secondary outcomes are Pittsburg Sleep Quality Index (PSQI), Oxygen Desaturation Index (ODI), Snoring Index (SI), Manual Assessment of Respiratory Motion (MARM), Breath Hold Test (BHT), and Self Evaluation of Breathing Questionnaire (SEBQ). The outcomes will be assessed at baseline and at the end of 12 weeks. A follow-up will be taken at the end of 24 weeks. Power analysis suggests that enrollment of 118 patients will required. Repeated measures ANOVA will be used to analyze the effect of the intervention.

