## Method

### Study design

The study design for the current protocol is an “assessor-blinded parallel group randomized controlled trial.” The trial will use the “Consolidated Standards of Reporting Trials (CONSORT) guidelines” [14]. All outcomes will be assessed at baseline and at the end of 12 weeks. Additionally, a follow-up will occur at the end of 24 weeks with assessment of daytime sleepiness, sleep quality, and breathing pattern dysfunction. The study flow is shown in Fig. 1. Reporting of the protocol is done according to the “Standard Protocol Items: Recommendations for Intervention Trials (SPIRIT) guidelines” [15]. The present study is approved by Institutional Research Committee (IRC) of Manipal Academy of Higher Education. Scientific Committee approval and ethical clearance to conduct the study is obtained from Manipal Hospital, Bangalore. The study is registered in Clinical Trials Registry–India (CTRI) (registration number—CTRI/2023/10/058486).

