### Participant recruitment, sample size, and eligibility criteria

According to the American Academy of Sleep Medicine (AASM) criteria, participants will be diagnosed with OSA by the consultant pulmonologist [16]. The recruitment of the participants will take place at Manipal Hospital, Bangalore, from October, 2023, to February, 2026.

The sample size was calculated at 5% level of significance with 80% power and an effect size of 0.30. The drop-out rate (20%) and the design effect (1.5) were also incorporated. Thus, the sample derived was 116.25 and 118 will be enrolled, with 59 in each group. The eligibility criteria are outlined in Table 1.

**Table 1 Tab1:** Eligibility criteria

Inclusion criteria	Exclusion criteria
Mild and moderate OSA (AHI ≥ 5 to ≤ 30)	Obstructive nasal diseases
Age 25 to 65 years	Craniofacial malformations
Either gender	Comorbid sleep disorders such as insomnia, restless leg syndrome
BMI less than 40 kg/m^2^	Pregnant women
	History of pharyngeal surgery
	History of congestive heart failure, cardiomyopathy, chronic obstructive pulmonary disease, and liver cirrhosis
	History of neuromuscular disorders such as myasthenia gravis, motor neuron disease, and demyelinating diseases
	History of stroke
	Psychiatric illness
	Consumption of alcoholic beverages (more than 3 oz/day or more than 2 alcoholic beverages/day)
	Periodontal disease (gingivitis]
	Temporomandibular joint dysfunction

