## Results

Statistician will be provided deidentified data, and analysis will be performed. Descriptive statistics (frequency tables and percentages for categorical variables and for computation of prevalence) will be used.

Mean/median and standard deviation/inter-quartile range will be analyzed after exploring skewness for the quantitative variables. Repeated-measures ANOVA or its non-parametric variants will be used after exploring the model assumptions to assess the effectiveness of the intervention. Correlation analysis may be done to explore associations between the outcomes.

Regression models may be used for adjustment of covariates to account the confounding factors and for unbiased treatment effect. Intention to treat analysis will be used to manage missing data. Inferential statistics will be used for exploratory data analysis.

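### Intention to treat is given as the missing-data method, but the only named analysis, classical repeated-measures ANOVA, would as written exclude participants with a missed visit

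*Protocol article*

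**What the plan says.** On missing data, the Results section of the protocol article says: "Intention to treat analysis will be used to manage missing data". It names no imputation method, no likelihood-based model and no assumption about why data are missing.

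On the effectiveness analysis, the same section says: "Repeated-measures ANOVA or its non-parametric variants will be used after exploring the model assumptions to assess the effectiveness of the intervention". The abstract agrees: "Repeated measures ANOVA will be used to analyze the effect of the intervention". Regression is optional and serves another purpose: "Regression models may be used for adjustment of covariates to account the confounding factors and for unbiased treatment effect".

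On expected losses, the section on recruitment, sample size and eligibility says: "The drop-out rate (20%) and the design effect (1.5) were also incorporated". Data monitoring and management adds only that withdrawals and losses are counted, with reasons.

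On visits, Study design says: "All outcomes will be assessed at baseline and at the end of 12 weeks". The 24-week follow-up then adds sleepiness, sleep quality and the breathing measures. AHI is not among the 24-week assessments.

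**The concern.** Intention to treat says that every randomised participant is analysed in the allocated arm. It does not say what stands in for a value that was never collected. The one missing-data rule in the article therefore cannot do the job it is given.

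The named analysis makes this matter. Classical repeated-measures ANOVA works on complete rows, so a participant missing any visit in the model is removed unless a value is filled in first. Without a further step, a result labelled intention to treat would rest on participants with complete data. For ESS, a primary outcome, someone who finished treatment and gave a week-12 score could be removed from the week-12 comparison for missing week 24. If those people differ in their week-12 response, and differ by arm, the comparison is biased.

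**Working it through.** **Inputs.** 5% significance, 80% power, effect size 0.30, drop-out 20%, design effect 1.5, derived sample 116.25, enrolment 118 (59 per arm), all from the sample-size section. Visit schedule from Study design.

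**1. The plan's own figure.** Assume that the 0.30 is Cohen's f, the test is the between-group F test of a repeated-measures ANOVA with m = 3 visits, and the correlation between visits is ρ = 0.5. The article states none of these. With non-centrality λ = N·f²·m / (1 + (m − 1)ρ), 80% power needs N = 62. Then:

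- 62 / (1 − 0.20) = 77.5
- 77.5 × 1.5 = 116.25, an exact match.

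With two visits and ρ = 0.5, N would be 68, which gives 68 / 0.80 × 1.5 = 127.5 and does not match. The match suggests a three-visit ANOVA but does not prove one. Dividing by 0.80 treats drop-outs as giving no analysable data.

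**2. How many could be excluded.** 118 × 0.20 = 23.6, about 24, leaving 94.4 (59 × 0.80 = 47.2 per arm). This is an upper figure for the planned 20%, because the article does not say by which visit the drop-out accrues.

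**3. Power.** After drop-out and the design effect, 118 × 0.80 / 1.5 = 62.9, still above the 62 required under the assumptions in step 1. Losing the drop-outs causes no shortfall in planned power.

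**4. Outcome by outcome.**

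| Outcome | Visits | Data that complete-row ANOVA would discard |
|---|---|---|
| ESS, PSQI, breathing measures | Baseline, week 12, week 24 | Week-12 values of anyone missing week 24, if all three visits enter one ANOVA |
| AHI, ODI, SI | Baseline, week 12 | Baseline values only |

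A participant without a week-12 AHI has no post-baseline AHI under any model, so a mixed model alone recovers little for that outcome.

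**5. Can discarding week-12 values bias the week-12 comparison?** This simulation is illustrative only; every setting is assumed. It used 4,000 simulated trials, 59 per arm, three visits, SD 1, ρ = 0.5 and no true effect. All participants have week 12. Loss before week 24 depends on the week-12 score in the CR arm (log-odds −1.5 + score) and is constant in the MFT arm (log-odds −1.5).

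- Average loss: 20.2%
- Week-12 difference in change, complete rows only: −0.096 SD
- The same difference, all week-12 values kept: −0.001 SD

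The false difference comes from throwing away observed data. Its sign follows from the assumed drop-out pattern and would reverse under the opposite pattern.

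**The case against.** The strongest reply is that the two sentences do not strictly contradict each other. Repeated-measures ANOVA run after imputation would satisfy both, and a statistical analysis plan that is not shown may name the imputation. The article never mentions complete cases, and its stated intention points the other way. This stands against the stronger reading, which a reader might infer, that the analysis will be complete-case. The documents support only that it would be if followed as written. The reply does not rescue the sentence itself, which gives intention to treat a task it cannot perform.

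Other objections stand in part:

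- The article does not say which visits enter the ANOVA. Week 24 is described as an additional follow-up, so the loss of week-12 ESS data depends on one three-visit model.
- The article says only that non-parametric variants may be used. Friedman's test has no between-arm factor and could not by itself test this design, and some rank-based longitudinal methods accept missing visits. The point is therefore confined to the classical ANOVA.
- A reader might infer that the CR arm will lose more participants because its programme is heavier. CR does have more components, but both arms exercise at the same daily and weekly frequency for 12 weeks, and nothing in the article predicts differential drop-out.

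**Conclusion.** The point holds in a limited form. The article's only missing-data rule defines an analysis set, not a method for missing values, and the only committed analysis would in its classical form drop participants with a missed visit. Up to about 24 of 118 could be excluded at the planned drop-out. The avoidable part is the discarding of week-12 ESS, PSQI and breathing data from people who miss week 24, which is conditional on all visits entering one ANOVA.

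The consequence is a risk of bias, and only if loss is related to the week-12 response and differs by arm. The documents do not allow its size or direction to be estimated; the simulated figure shows only that the mechanism works. A reader might also infer a loss of planned power, or that the AHI comparison is damaged in the same way. Neither follows: drop-out is already in the sample size, and AHI has no later visit whose absence would remove a collected week-12 value. AHI still needs a stated method for missing week-12 values, because intention to treat does not provide one.

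**What to change.** Replace the missing-data sentence in Results with:

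> All randomised participants are analysed in their allocated arm. Outcomes with three visits are analysed with a likelihood-based mixed model for repeated measures (arm, visit, arm-by-visit, baseline value) using all available data, with the week-12 contrast reported from that model. Week-12 AHI is analysed with adjustment for baseline AHI, with multiple imputation of missing week-12 values and a sensitivity analysis for data not missing at random.

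In the mixed model, weeks 12 and 24 are the outcome visits and baseline is a covariate. Someone with no post-baseline value adds no outcome information to it. If the non-parametric fallback is kept, name the method and say how it treats a missed visit. Settle this before outcome data are analysed, so that the method is not chosen after results are seen.

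The cost is a change of wording and slightly more analysis work. There are no new data, no extra visits and no change to 118. The main analysis would rest on a missing-at-random assumption, which the AHI sensitivity analysis tests for that outcome only.

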## Discussion

The current study includes functional nasal breathing rehabilitation along with myofunctional therapy and diaphragmatic breathing as a comprehensive management protocol for patients with OSA. Myofunctional therapy as a part of conventional treatment for OSA, in addition to CPAP, has reported to have a positive effect on the tone of oropharyngeal muscles and other soft tissues of the upper airway [11]. It may be hypothesized from the preceding research that functional nasal rehabilitation and diaphragmatic breathing exercise may be beneficial for patients with OSA [13, 18]. 

A limitation of this study as designed is that it will be performed in a specific region, and the data cannot be generalized to other populations and settings.

## Data Availability

The present study has no data.
